## Abstract

**Background:**

Refugees often report high levels of psychological distress due to traumatic experiences before and during flight as well as many post-migration stressors. Refugees with hazardous substance use or existing substance use disorder (SUD) are a particularly vulnerable group for whom few preventive and therapeutic measures are available. The aim of this study is to investigate the effectiveness of an integrative culturally sensitive group therapy approach (STARC-SUD) to improve affect regulation in refugees with substance-related problems.

**Methods:**

The study aims to include *N* = 286 male refugees with psychological distress (GHQ-12 > 13) and hazardous substance use or SUD (AUDIT > 7 or DUDIT > 6). Therapists working supported by interpreters will deliver the STARC-SUD intervention in addiction aid facilities in six metropolitan regions of Germany. The primary endpoint is severity of psychological distress (GHQ-12). The effectiveness of STARC-SUD is compared with treatment as usual (TAU) post-intervention and 3 months later.

**Discussion:**

This trial will be one of the first RCTs on a culturally sensitive transdiagnostic intervention for trauma-exposed refugees with hazardous substances or SUD. The trial might gain new insights into the efficacy of such an intervention.

**Trial registration:**

OSF Registry osf.io/nhxd4. Registered prospectively on September 22, 2020, doi: 10.17605/OSF.IO/NHXD4. DRKS DRKS00017668

## Administrative information

Note: The numbers in curly brackets in this protocol refer to the SPIRIT checklist item numbers. The order of the items has been modified to group similar items (see http://www.equator-network.org/reporting-guidelines/spirit-2013-statement-defining-standard-protocol-items-for-clinical-trials/).

## Introduction

### Background and rationale {6a}

Relationships between hazardous substance use or substance use disorders (SUD) and mental disorders have been well documented [1]. Individuals with comorbid mental disorders related to post-traumatic stress may find themselves rejected from both mental health care programs and addiction services [2]. It has therefore been recommended to integrate SUD services for refugees with mental health services when offering care for refugees with SUD [3]. Adequate interventions for refugees with hazardous substance use or SUD and co-occurring post-traumatic psychological distress are urgently needed.

Very few studies investigated the effects of substance use interventions in refugee populations. A recent randomized controlled trial (RCT) among Somali refugees living in Kenya suggested small effects of a standardized brief intervention to reduce Khat use in this population [4]. The intervention was less effective in participants with comorbid psychopathology, particularly in patients with PTSD. Another RCT examined the effects of the “Common Elements Treatment Approach (CETA),” a transdiagnostic treatment for comorbid disorders in refugees in Thailand [5]. Moderate to large symptom reductions were observed for depression, anxiety, and post-traumatic stress, but not for alcohol use. Taken together, the existing studies suggest that more evidence on the efficacy of interventions for refugees with SUD is needed. Neither a brief SUD treatment alone nor a psychotherapeutic approach without SUD treatment had a sufficient effect on both, problematic substance use and comorbid psychological symptoms.

In non-migrant populations with SUD and post-traumatic symptoms, low-threshold integrative interventions are effective in reducing psychological distress and emotion dysregulation. For example, a recent RCT on the effects of a low-threshold stabilizing integrated group treatment for SUD and PTSD in a non-migrant population was compared to usual SUD relapse prevention and to a waitlist control group for women with SUD and PTSD [6]. The results of this study revealed a significantly greater reduction in psychological distress in patients that received the integrative intervention compared to patients on the waitlist at post-treatment (*d* = 0.39), which was sustained at 3- and 6-month follow-up. Such interventions should be culturally adapted and, given the spectrum of psychological symptoms among refugees (e.g., PTSD, anxiety disorders, depression [7]), take a transdiagnostic approach that targets underlying vulnerabilities (e.g., [8]).

Recently, a culture-sensitive transdiagnostic cognitive-behavioral group therapy for refugees (STARC) has been developed that aims at reducing psychological distress by focussing on emotion regulation and has been successfully tested for feasibility [9]. However, refugees with hazardous substance use or SUD might need an intervention that additionally considers problematic substance use or SUD. However, such an intervention has not been developed and evaluated yet. Therefore, the aim of this study is to develop and examine the effects of a transdiagnostic integrative group intervention for refugees with hazardous substance use or SUD and co-occurring psychological distress (STARC-SUD) on reducing refugees’ psychological distress.

### The need for a trial

Both addiction treatment facilities and institutions providing mental health care for refugees in Germany are confronted with the challenge to provide adequate care for individuals with psychological distress as a consequence of traumatic experiences and additional hazardous substance use or SUD that complicates treatment. Adequate interventions for this target group are urgently needed. If the “Skills Training in Affect Regulation – a Culture-sensitive Approach in refugees with Substance Use Disorder” (STARC) intervention, adapted for refugees with substance use or SUD, will prove to be effective, the intervention might help to provide evidence-based treatment for refugees with trauma exposure and substance use problems.

### Objectives {7}

The primary objective is to determine if STARC-SUD is more effective in reducing psychological distress in refugees with trauma exposure and substance use problems. It is hypothesized that STARC-SUD is more effective in reducing psychological distress than treatment as usual, i.e., the care that they would usually receive from SUD and/or refugee counseling or treatment centers. The secondary objective is to compare the effectiveness of STARC-SUD versus treatment as usual in reducing emotion dysregulation, substance use, and symptoms of PTSD.

### Trial design {8}

This study is a multicenter, randomized controlled, outcome adjudicator-blinded superiority trial with two parallel groups and a primary endpoint of psychological distress post-treatment to compare the effectiveness of STARC SUD (“Skills Training in Affect Regulation – a culture-sensitive approach”) versus treatment as usual in trauma-exposed refugees with substance use problems. The randomization will be performed in blocks of 8 with a 1:1 allocation to one of the two treatment arms. Randomization numbers will be assigned to eligible study participants in ascending order of their inclusion.

## Methods: participants, interventions, and outcomes

### Study setting {9}

Participants will be recruited in six metropolitan regions of Germany (Hamburg, Bremen, Berlin, Hannover, Frankfurt, München). The intervention is conducted in SUD counseling and treatment centers in the six metropolitan regions.

### Eligibility criteria {10}

The following are the inclusion criteria: (1) psychological distress (GHQ-12 > 13); (2) hazardous substance or SUD (AUDIT > 7, DUDIT > 6); (3) exposure to traumatic experiences (e.g., war, persecution, torture, or traumatic experiences during flight; PCL-5); (4) asylum seeker or refugee (e.g., Afghanistan, Syria, Iraq); and (6) male gender. The following are the exclusion criteria: (1) acute psychosis and (2) acute suicidality.

### Who will take informed consent? {26a}

Information sheets about the study and consent forms are provided for all participants involved in the trial. The information sheets and consent forms have been written in easy language and have been translated into Arabic, Farsi, and English. The research personnel will introduce the trial and inform the participants about its main aspects. The research personnel will then discuss the trial with the participants in light of the information provided. If the participant is eligible and willing to participate in the trial, the research personnel will obtain written consent from the participant.

### Additional consent provisions for collection and use of participant data and biological specimens {26b}

On the consent form, participants will be asked if they agree to the use of their data. Participants will be asked for permission for the research team to share relevant data with people taking part in the research or from regulatory authorities, where relevant. This trial does not involve collecting biological specimens.

### Interventions

#### Explanation for the choice of comparators {6b}

A treatment as usual (TAU) control group is used to compare the experimental intervention to treatments that are already used in clinical practice. Patients in the TAU group will not be offered any additional specific intervention other than the care that they would usually receive from SUD and/or refugee counseling or treatment centers or their general practitioner.

#### Intervention description {11a}

The intervention (STARC-SUD) is tailored to the needs of refugees with SUD and additional psychological distress. STARC-SUD is an adaption of Skills-Training of Affect Regulation – a Culture-sensitive Approach (STARC) [10], a culturally sensitive group intervention developed for refugees in Western middle- or high-income countries. The intervention is based on elements from skills-based treatments (e.g., Skills Training in Affective and Interpersonal Regulation therapy (STAIR [11];), Dialectic Behavioral Therapy (DBT [12];), and Culturally Adapted Cognitive Behavioral Therapy (CA-CBT [13];)). The authors developed the STARC program according to guidelines for developing culturally sensitive interventions [14]. The manual includes culture-sensitive metaphors and expressions and uses easy language. A pilot study on Afghan refugees indicated preliminary evidence that the intervention reduces difficulties in emotion regulation, general distress, and post-traumatic stress disorder symptoms [9].

For this trial, STARC was adapted for refugees with SUD [15]. The conceptual framework of Heim and Kohrt was used for the adaptions [16]. The results of five focus group discussions with refugees on concepts of SUD and their treatment informed the adaption. An expert group suggested adaptions and decided by consensus on their implementation. Two pilot groups were conducted with the adapted STARC-SUD program. Interviews with the therapists of these pilot groups informed further adaption.

#### Criteria for discontinuing or modifying allocated interventions {11b}

In case of a serious adverse event, the PI will decide together with a Study Safety Board if the treatment needs to be discontinued. Participants are free to discontinue or modify the allocated intervention at any time of the study. In case of worsening disease (e.g., acute suicidality), the study personnel will consult the participant on additional necessary treatment and referral options.

#### Strategies to improve adherence to interventions {11c}

All study therapists were trained in the provision of the intervention prior to the start of the study. To ensure fidelity of treatment, the provision of treatment will be highly standardized (use of a manual, intensive training of all therapists by the authors of the STARC-SUD program, and on-going supervision). Adherence will be further assured through regular therapist meetings.

#### Relevant concomitant care permitted or prohibited during the trial {11d}

Concomitant care is permitted for both groups.

#### Provisions for post-trial care {30}

There is no anticipated harm to trial participation.

### Outcomes {12}

The primary outcome will be the severity of psychological distress as measured with the General Health Questionnaire-12 (GHQ-12) [17] at *t*_1_ (post-treatment) and *t*_2_ (3-month follow-up).

The following are the secondary outcomes: severity of emotion dysregulation will be assessed at *t*_0_, *t*_1_, and *t*_2_ using the Difficulties in Emotion Regulation Scale (DERS) [18]. Substance use will be assessed by using the Alcohol Use Disorders Identification Test (AUDIT) [19] and the Drug Use Disorders Identification Test (DUDIT) [20] at *t*_0_, *t*_1_, and *t*_2_. Substance use within the last 30 days will be assessed at *t*_0_, *t*_1_, and *t*_2_ using the Addiction Severity Index-Lite (ASI-Lite) [21]. Symptoms of PTSD will be assessed at *t*_0_, *t*_1_, and *t*_2_ using the PTSD Checklist for DSM-5 (PCL-5) [22].

#### Participant timeline {13}

Potential participants who self-refer or are referred by collaborating services will be invited for an eligibility assessment by a study therapist at one of the trial locations. Potential participants will receive information about the trial and an information sheet and will have the possibility to ask questions. The information sheet provides information about the aims of the study, the clinical assessment and random allocation process, treatment, and assessment schedule with details of time involved, potential benefits and risks of taking part, ethical approval, funding information, data management and confidentiality, freedom to withdraw at any time, financial reimbursement, and contact details. Afterwards, the potential study participant will be invited to a short interview with the study therapist to screen for major inclusion and exclusion criteria (e.g., substance use problems). Potential eligible participants will be invited to conduct a 1–2-h *t*_0_ assessment with the study personnel to assess all the inclusion and exclusion criteria and additional baseline characteristics. This will include assessment of sociodemographic variables (gender and asylum/residence status), general psychological distress (General Health Questionnaire-12 (GHQ-12)), alcohol use (Alcohol Use Disorders Identification Test (AUDIT)), substance use (Drug Use Disorders Identification Test (DUDIT)), trauma exposure (trauma exposure section of the PTSD Checklist for DSM-5 (PCL-5)), and a clinical evaluation of acute suicidality and psychosis using purpose-designed items. Eligible participants that agree to participate will sign the informed consent form for the trial. Those who are not eligible or do not agree to participate in the trial will be advised about alternative treatment options.

In addition to this *t*_0_ assessment, the participants will be assessed at end of treatment (*t*_1_) and 3 months later (*t*_2_; Fig. 1). All assessments will be conducted with e-CRFs in the language most appropriate for the respective participant (e.g., Arabic, Farsi, English, German) using tablet computers. The study personnel will assist with the data assessments. Translators will assist with the data assessment, will translate the questions if necessary, and will verify that all questions are correctly understood.

**Fig. 1 Fig1:**
[figure not shown]
Schedule of enrollment, interventions, and assessments. GHQ-12, General Health Questionnaire-12; DERS, Difficulties in Emotion Regulation Scale, post-traumatic anger; DAR-5, Dimensions of Anger Reactions Scale-5; AUDIT, Alcohol Use Disorders Identification Test; DUDIT, Drug Use Disorders Identification Test; ASI-Lite, Addiction Severity Index-Lite; PCL-5, PTSD Checklist for DSM-5; GAD-7, Generalized Anxiety Disorder 7; PHQ-9, Patient Health Questionnaire; PMLD, Migration Living Difficulties Checklist

The *t*_0_, *t*_1_, and *t*_2_ assessment will include the substance use section of the Addiction Severity Index (substance used within the last 30 days), PTSD symptoms (PTSD Checklist for DSM-5 (PCL-5)), anxiety symptoms (Generalized Anxiety Disorder 7 (GAD-7)), depression symptoms (Patient Health Questionnaire (PHQ-9)), emotion dysregulation (DERS, DAR-5), quality of life (World Health Organization Quality of Life Scale (WHOQOL-BREF)), post-migration stressors (PMLD; Silove et al. (1998), and purpose-designed items on therapy expectations.

#### Sample size {14}

*N* = 286 participants are planned to be included in the study. An earlier RCT comparing a transdiagnostic group intervention for refugees vs. treatment as usual found a greater reduction in psychological distress (as measured by GHQ-12) in the intervention group compared with the control group, with a medium effect size of *d* = 0.57 in the change from baseline to 3-month follow-up [23]. A pilot study of STARC showed that the recruitment of refugees with psychological distress was feasible, with about 85% of the screened patients being eligible for the study [9].

In a previous study evaluating the effects of an integrated present-focused treatment of SUD and PTSD, we found a greater reduction in psychological distress (as measured by SCL-27) in the intervention group compared with the control group, with a mean effect size of *d* = 0.39 [6]. On the basis of these results, we assume a small to medium effect size of *d* = 0.40 for STARC-SUD compared to TAU in a sample of refugees with SUD and co-occurring psychological distress. To detect between-group differences of an effect size of *d* = 0.40 (*α* = 0.05; power = 0.80), 100 participants per group are required. To account for a dropout rate of 30%, we aim to recruit 286 participants.

#### Recruitment {15}

To include 286 individuals, participants will be recruited from SUD counseling and/or treatment centers in 6 metropolitan regions of Germany (Hamburg, Bremen, Berlin, Hannover, Frankfurt, München). Participants will be recruited by promotional print material, videos, blogs, personal presentations in refugee camps, SUD treatment, and counseling centers, via advertisements in magazines, on websites, and on social media.

Assuming that about two-thirds (67%) of the screened refugees will be eligible, and about two-thirds (67%) of the eligible refugees will agree to participate, approximately 5 refugees per month need to be screened in each center, and about 4 participants per quarter (16 per 12 months) need to be randomized at each of the 6 sites to include 286 patients. The approx. enrollment period will span 36 months.

### Assignment of interventions: allocation

#### Sequence generation {16a}

The allocation sequence was generated by computer-generated random numbers using R. Participants are randomly assigned to either the control or the experimental group with a 1:1 allocation as per a computer-generated randomization schedule stratified by site using blocks of random sizes. The block sizes will not be disclosed to ensure concealment.

#### Concealment mechanism {16b}

The random number is sequentially ordered and will be allocated in ascending order. The study personnel will allocate the next random number to the next eligible participant by accessing a web-based random platform in which the random sequence is stored. The allocation sequence is concealed, as the web-based platform will not release the randomization code until the patient has been recruited into the trial.

#### Implementation {16c}

The allocation sequence was generated by a researcher not involved in the recruitment process of this study. Participants will be enrolled after the eligibility assessment by the study personnel who will inform the participant about group allocation. A response form will be sent to the study therapist who is not involved in evaluating the results of the study. The staff responsible for the data analysis will not receive information about the group assignment.

### Assignment of interventions: blinding

#### Who will be blinded {17a}

The outcome adjudicators will be blinded for the assignment of interventions. For feasibility reasons, the data assessors will be only blinded at the *t*_0_ assessment in the participating sites. Assessors will be trained in a standardized assessment procedure (e.g., adhering to the identical questions) to reduce bias related to unblinding.

#### Procedure for unblinding if needed {17b}

Data assessors are only blinded for the *t*_0_ baseline assessment for feasibility reasons. Only the data adjudicators are blinded for all assessments and will not be unblinded before the end of the data analysis. As the remaining study personnel is unblinded, an unblinding procedure will not be necessary for this study.

### Data collection and management

#### Plans for assessment and collection of outcomes {18a}

The coordinating site will be responsible for the organization of the data assessment at the different study sites. The data management team of CIAR will prepare the study measures and perform the programming of measures for data entry via tablets, the data verification, the data cleaning, the plausibility checks, and the regular control of data quality.

Study instruments will include the General Health Questionnaire-12 (GHQ-12), Alcohol Use Disorders Identification Test (AUDIT), Drug Use Disorders Identification Test (DUDIT), PTSD Checklist for DSM-5 (PCL-5), Difficulties in Emotion Regulation Scale (DERS), Dimensions of Anger Reactions Scale-5 (DAR-5), Addiction Severity Index Lite (ASI-Lite), General Anxiety Disorder (GAD-7) Questionnaire, Patient Health Questionnaire-9 (PHQ-9), Post Migration Living Difficulties Checklist (PMLD), WHO Quality of Life Scale Abbreviated Version (WHOQOL-BREF), and serious adverse events (SAEs; German: SUEs).

Psychological distress is assessed by the General Health Questionnaire-12 (GHQ-12 [24]). It aims to measure the current and recent general health over the last few weeks. The GHQ-12 consists of 12 items which are rated on a 4-point response scale. It has shown good psychometric properties in regard to reliability and validity in general health care settings with patient samples, making this short screening instrument work as well as its longer version [24].

Alcohol use is assessed by the Alcohol Use Disorders Identification Test (AUDIT [19]). The AUDIT consists of 10 items and aims to assess past-year hazardous drinking, harmful alcohol use, and alcohol dependence. Eight items are rated on a 5-point scale, and 2 items are rated on a 3-point scale all ranging between 0 and 4. A total score can be derived from summarizing all items. Higher values represent higher levels of problematic alcohol use [19]. The AUDIT has shown good psychometric properties, such as test-retest reliability and internal consistency, in a variety of settings [25].

Drug use is assessed using the Drug Use Disorders Identification Test (DUDIT [26]). The DUDIT contains 11 items and aims to assess past-year substance use disorders of a wide variety of drugs. Nine items are rated on a 5-point scale, and 2 items are rated on a 3-point scale. The DUDIT has shown good measures of reliability and validity in clinical settings and research [27].

Symptoms of PTSD will be assessed by using the PTSD Checklist for DSM-5 (PCL-5 [22]) including the Life Events Checklist for DSM-5 (LEC-5) and Criterion A. The PCL-5 is a 20-item self-report measure assessing the 20 symptoms of PTSD described in DSM-5 over the past month. It is used for monitoring symptom change during and after treatment, screening individuals for PTSD, and making a provisional PTSD diagnosis. Items are ranked on a 5-point Likert scale ranging from 0 to 4. Sum scores will be used for analyses [22]. The PCL-5 is valid and reliable, useful in determining symptom severity, and sensitive to symptom change among military servicemembers and undergraduate student samples [22].

Emotion dysregulation will be monitored by using the Difficulties in Emotion Regulation Scale (DERS [18]). Participants rate all of the 36 items on a 5-point Likert scale. The scale focuses on adaptive ways of responding to emotional distress and can be categorized into 6 subscales ((a) lack of emotional awareness, (b) lack of emotional clarity, (c) difficulty regulating behavior when distressed, (d) difficulty engaging in goal-directed cognition and behavior when distressed, (e) unwillingness to accept certain emotional responses, (f) lack of access to strategies for feeling better when distressed). Higher scores indicate more difficulties in emotion regulation. According to the preliminary findings, the DERS shows high internal consistency, good test-retest reliability, and adequate construct and predictive validity in undergraduate student samples [18].

Anger reaction is assessed using the Dimensions of Anger Reactions Scale-5 (DAR-5 [28];. This shortened version aims to measure five anger experiences (frequency, intensity, duration, antagonism towards others, social relation interference) of the past 4 weeks on a 5-point Likert scale ranging from 1 to 5. The DAR-5 has shown strong internal reliability and good validity in a college student sample with and without a history of trauma exposure [29] and in a male veterans sample with PTSD [28].

Additionally, substance use within the last 30 days will be assessed by using parts of the Addiction Severity Index Lite (ASI-Lite [21]). Participants will be asked in an interview to indicate how many days within the last 30 days they have used a given list of substances, the form of drug application, the age when they first started using the substance regularly, and for how many years they used the substance regularly [21]. The ASI-Lite is a short version of the ASI, which has shown to be a reliable and valid instrument with a wide range of clinical and research applications [30].

Anxiety is assessed using the General Anxiety Disorder (GAD-7 [31]) questionnaire. The GAD-7 is a brief seven-item self-report questionnaire, ranging from 0 to 3, that aims to identify probable cases of generalized anxiety disorder (GAD) and its severity in clinical practice and research by assessing the patients’ health status over the past 2 weeks. It has shown to have good internal consistency, test-retest reliability, and criterion, construct, and factorial and procedural validity in clinical settings [31].

The Patient Health Questionnaire-9 (PHQ-9 [32]) is the depression module of the full Patient Health Questionnaire (PHQ). The PHQ-9 aims to measure depression and its severity over the past 2 weeks in clinical practice and research. It consists of nine items plus an additional item if problems were checked off on the other items, and each of the 9 DSM-IV criteria are ranging from 0 to 3. Its measurement of depression severity has shown to be reliable and valid in clinical settings [32].

The Post Migration Living Difficulties (PMLD [33] checklist assesses the current post-migration stressors of asylum seekers. It is a self-report questionnaire with 24 items measuring the severity of different post-migration problems on a 5-point scale. It comprises difficulties experienced in the host country over the past 12 months or since arrival, if less than 12 months ago [33]. The items each measure a different experience, making reliability not relevant [34]. However, research has shown that the checklist can differentiate between asylum seekers and refugees with different residency statuses and can be used as a predictor of mental health in displaced population samples [33, 35, 36].

Quality of life is assessed using the WHO Quality of Life Scale Abbreviated Version (WHOQOL-BREF [37]). The WHOQOL-BREF is a 26-item self-report questionnaire including four domains of quality of life (physical health, psychological health, social relationships, environment), overall quality of life, and general health. It assesses the quality of life of the past 2 weeks on a 5-point Likert scale ranging from 1 to 5. The WHOQOL-BREF has shown good internal consistency, test-retest reliability, discriminant validity, and content validity in different subject samples with and without current health problems [37].

We will monitor and assess (serious) adverse events with a standardized report form during post-intervention and the 3-month follow-up. Any adverse events or reactions that are considered to be related to the intervention will be recorded, managed, and reported to the study coordinator. Serious adverse events will be reported to the ethics committee within 24 h of occurrence, and the study will be terminated prematurely.

The study assessors were trained to conduct the standardized assessment procedures prior to the start of the study.

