#### Safety

A *χ*^2^ test will be applied to compare the number of SAE between the two groups. Severity and relationship to treatment will be descriptively summarized in tables by group.

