#### Adverse event reporting and harms {22}

A serious adverse event (SAEs) for this study is any untoward medical occurrence that is believed by the investigators to be causally related to the study intervention and results in any of the following: life-threatening condition (that is, immediate risk of death), severe or permanent disability, and prolonged hospitalization. SAEs will be collected after the participant has provided consent and enrolled in the study. All SAEs occurring after the entry into the study will be recorded. To ensure participant safety, every SAE, regardless of suspected causality, occurring after the subject has provided informed consent until the subject has stopped study participation, must be reported by the sites to the PI within 24 h of learning of its occurrence. The investigators of the sites take the responsibility for appropriate reporting of SAEs. In case of a SAE, discontinuation will be decided by consensus of PI, local investigator, and the Study Safety Board. The main concern will be the safety of the study subjects.

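### The outcome-collection section ends the study automatically on a serious adverse event, contradicting the case-by-case decision in the harms section

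*Protocol article*

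**What the plan says.** Five places in the Protocol article bear on what follows an SAE.

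- **Plans for assessment and collection of outcomes {18a}**, after the list of instruments: SAEs are reported to the ethics committee within 24 h "of occurrence, and the study will be terminated prematurely".
- **Adverse event reporting and harms {22}**: "In case of a SAE, discontinuation will be decided by consensus of PI, local investigator, and the Study Safety Board". The same section says "All SAEs occurring after the entry into the study will be recorded". It defines an SAE as an event "believed by the investigators to be causally related to the study intervention", yet asks sites to report every SAE whatever its suspected cause.
- **Criteria for discontinuing or modifying allocated interventions {11b}**, on whether a participant's treatment stops: "In case of a serious adverse event, the PI will decide together with a Study Safety Board if the treatment needs to be discontinued".
- **Safety**, under the statistical methods: a chi-square "test will be applied to compare the number of SAE between the two groups", and "Severity and relationship to treatment will be descriptively summarized in tables by group".
- **Sample size {14}**: "To account for a dropout rate of 30%, we aim to recruit 286 participants".

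**The concern.** The same trigger, an SAE, leads to an automatic end in one section and to a deliberated decision in two others. A site that reads {18a} and a site that reads {22} would act differently, and nothing in the protocol says which text prevails.

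On the literal reading the whole trial is at stake: one event could close it before the primary question is answered. On the narrower reading, where the participant rather than the study was meant, the stake is that a person could be taken out without the judgement that {11b} and {22} call for.

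**Working it through.** **1. Setting the sections side by side**

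| Section | Trigger | Consequence | Who decides |
|---|---|---|---|
| {18a} | SAE | the study ends early | nobody named; automatic |
| {22} | SAE | discontinuation, object not stated | PI, local investigator, Study Safety Board, by consensus |
| {11b} | SAE | possible end of treatment | PI with Study Safety Board |

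Section {22} does not say whether discontinuation refers to the participant's treatment or to the trial. If the trial, it contradicts {18a} directly. If treatment, {18a} leaves that decision without purpose, because the study would already be over. Neither meaning reconciles the two. Section {11b} speaks only of treatment, so it is the weaker witness: it does not fit {18a} but does not address ending the study. The main contradiction is between {18a} and {22}.

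**2. Fit with the rest of the plan**

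Recording all SAEs and comparing their numbers by arm both assume that the trial carries on after an SAE. That conflicts with {18a} if the study ends. It does not conflict if only one participant's involvement ends, since the event is still counted in its arm.

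**3. The plan's own figure**

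For d = 0.40, two-sided alpha 0.05 and power 0.80, the t-test calculation gives 99.08 per group, which rounds up to the stated 100. Allowing 30% dropout, 100 / 0.70 = 142.9, so 143 per group and 286 in total. The figure reproduces and this point does not affect it. The dropout allowance is 286 − 200 = 86 participants.

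**4. Can the effect be sized?**

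The protocol gives no SAE rate. For an **assumed** per-participant risk p, independent across participants, the chance of at least one SAE is 1 − (1 − p)^286, and the expected number of participants with an SAE is 286 × p.

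| Assumed p | Chance of at least one SAE | Expected participants with an SAE |
|---|---|---|
| 0.1% | 25% | 0.29 |
| 0.5% | 76% | 1.43 |
| 1% | 94% | 2.86 |
| 2% | 99.7% | 5.72 |
| 5% | over 99.9% | 14.3 |

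The middle column runs from one in four to near certainty, depending only on the assumption, so it settles nothing about how likely the clause is to be triggered. The last column is more useful for the participant-level reading: over the whole assumed range, automatic exits are few beside the 86 losses already allowed for.

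**The case against.** The best defence is that this is loose wording. The clause is the tail of a sentence in a section about measurement instruments. The sections that govern the matter, {11b} and {22}, both make it a decision, and the safety analysis expects SAEs in both arms. The authors probably meant that the participant's involvement ends, or that the study may be stopped. This is plausible, and it lowers the weight of the point. It does not remove it: the sentence says the study, says it will end, and is contradicted rather than qualified elsewhere. Nor does the point turn on something an article leaves to a fuller document; it concerns a rule that is stated.

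It could also be said that SAEs are defined as causally related and so will be rare. But the consensus rule in {22} applies to those same events, and its reporting sentence covers events of any cause, so the conflict remains.

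Two stronger readings are tempting.

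- **A reader might infer that the trial is likely to be stopped by this clause.** The documents do not support that. They give no SAE rate, the section on post-trial care {30} anticipates no harm, and if only related events count the risk could lie below any value assumed above.
- **A reader might infer that the clause makes the SAE test worthless.** For k SAEs against 0 in arms of 143, the uncorrected chi-square is 286k / (286 − k). One against none gives 286/285 = 1.00, p = 0.32; three against none gives 858/283 = 3.03, p = 0.08; four against none gives 1144/282 = 4.06, p = 0.044. At assumed risks of 0.1% to 2%, only 0.3 to 5.7 participants with an SAE are expected in all, so the test would be nearly uninformative over most of that range even with the clause deleted. The sparse events are the cause, not the clause.

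**Conclusion.** The inconsistency is certain; its practical consequence is not. As written, {18a} prescribes an automatic end to the study that {22} contradicts and that does not fit {11b}. Only the literal reading threatens the trial and clashes with recording and comparing SAEs. The participant-level reading leaves the safety comparison intact and adds little missing data, a judgement that rests on assumed SAE risks of up to 5%, not on a rate in the protocol.

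This is an internal inconsistency in a safety rule. It should be corrected because it gives sites two incompatible instructions for a serious event, but it is not a flaw in the design, the sample size or the primary analysis, and it does not rank among the most serious points.

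**What to change.** In {18a}, delete the part of the sentence after the comma, which terminates the study. State instead that SAEs are reported, that any discontinuation is decided as set out in {11b} and {22} by the PI, local investigator and Study Safety Board, and that no SAE ends the study automatically. Naming all three parties matters, because {11b} omits the local investigator whom {22} includes.

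Nothing more is needed to remove the contradiction. A separate rule for stopping the whole trial, or one on continuing t1 and t2 assessments after an SAE, would be an addition for the investigators to consider.

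The cost is a short clarification notified to sites and the ethics committee. Sample size and analysis are unchanged.
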